### Rationale

Periodontitis can lead to the development of infrabony defects and periodontal pockets, resulting in the loss of the attachment apparatus. This can pose a significant problem.

Therefore, the main objective of regenerative therapy is to regenerate the periodontal attachment.

Two distinct approaches will be used: ASB and autologous PRF combined with OCP-DBBM. ASB is a bone graft that hardens physiologically and becomes integrated within the fibrin network. Autologous PRF with OCP-DBBM uses macroporous octacalcium phosphate–coated deproteinized bovine bone. This composite material offers both osteoconductive and osteoinductive properties, making it highly suitable for bone regeneration.

### Objectives

The following are the objectives of this study:

Objective 1: to assess the efficacy of ASB in infrabony defects at 6 months after surgery with regard to radiographic bone fill, reduction in probing pocket depth (PPD), and increase in clinical attachment level (CAL).Objective 2: to assess the efficacy of autologous PRF in conjunction with OCP-DBBM in infrabony defects at 6 months after surgery with regard to radiographic bone fill, reduction in PPD, and increase in CAL.Objective 3: to assess the efficacy of ASB and autologous PRF in conjunction with OCP-DBBM in infrabony defects at 6 months after surgery with regard to radiographic bone fill, reduction in PPD, and increase in CAL.

## Methods

### Recruitment

The selection of study participants was performed using well-defined inclusion and exclusion criteria to ensure uniformity and reliability of clinical outcomes. Only systemically healthy individuals diagnosed with chronic periodontitis and presenting with specific radiographic and clinical characteristics were enrolled. The inclusion criteria were designed to identify patients with distinct infrabony periodontal defects that could be assessed radiographically and managed surgically, thereby enabling accurate evaluation of regenerative outcomes. Each participant was selected after completion of initial nonsurgical periodontal therapy and demonstration of acceptable oral hygiene maintenance.

The inclusion parameters emphasized the presence of at least 1 or 2 well-defined infrabony defects with probing depth and clinical attachment loss of ≥5 mm, ensuring adequate disease severity for evaluating regenerative potential. Radiographic criteria, such as a defect depth ≥3 mm and a base positioned ≥3 mm coronal to the root apex, were essential to avoid endodontic involvement and to ensure sufficient bone support for defect containment. The requirement of a minimum of 3 mm of keratinized gingiva around the test tooth ensured soft-tissue stability and favorable surgical access.

The exclusion criteria were framed to eliminate potential confounding variables that could affect periodontal healing or regenerative outcomes. Patients with stage 4 grade C periodontitis, poor plaque control (plaque index >1), or smoking habits were excluded due to their known adverse effects on periodontal regeneration. Similarly, teeth exhibiting mobility greater than grade 2, advanced furcation involvement (class 3 or 4), or prior periodontal surgery in the same quadrant were omitted to maintain site comparability. Pregnant and lactating women were also excluded to prevent any ethical or physiological risks associated with surgical intervention and medication use.

These stringent criteria collectively will ensure that all participants meet the clinical and radiographic prerequisites for reliable assessment of treatment efficacy while minimizing biological and procedural variability (Textbox 1).

The sample size calculation was as follows:

[figure not shown]

where α=.05, β=.1, SD in group 1 (σ1) is 0.83, mean in group 1 (μ_1_) is 0.522, SD in group 2 is (σ2) 0.044, mean in group 2 (μ_2_) is 0.42, and ratio (group 2 to group 1)=1. The total sample size required was 10 participants per group, as indicated by the calculation [13].

Inclusion and exclusion criteria for patient screening for infrabony defects.

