### Statistical Analysis

#### Power

PI, papillary bleeding index, PPD, relative attachment level, and relative gingival marginal level will be calculated by mean and SD values. Statistical tests such as the paired 1-tailed *t* test or Wilcoxon signed-rank test for within-group comparison and the ANOVA or Kruskal-Wallis test for between-group comparison are typically used to assess clinical and radiographic outcomes. The choice of test depends on whether the data follow a normal distribution. The difference between radiographic bone fill, PPD, CAL and relative gingival margin level will be considered significant only if *P*<.05.

The study population will be divided into 2 groups: group 1 (ASB) and group 2 (autologous PRF with OCP-DBBM). There are no subgroups in the study.

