### Comparison With Prior Work

Singh and Kashyap [13] conducted a clinical study comparing ASB and a mixture of autologous PRF and bioactive glass (PRF-BG) for regenerating periodontal infrabony defects. They found that, unlike other platelet concentrates, PRF and CGF do not need external anticoagulants and release growth factors that aid healing. However, CGF and PRF alone cannot retain bone graft material long enough for proper healing. To improve bone graft stability, they tested 3 therapies (open flap debridement [OFD], PRF-BG, and ASB). The graft materials were well tolerated, and PRF-BG and ASB groups showed reduced postoperative inflammation compared with the OFD group.

Najeeb et al [8] conducted a clinical study comparing the resolution of infrabony defects and bone regeneration in three-walled defects treated with OFD using either OCP-DBBM (Ti-oss) or DFDBA. Based on CBCT analysis, they concluded that Ti-oss demonstrated superior regenerative outcomes.

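### The printed planning values, with a group 1 SD of 0.83, are incompatible with the stated 10 participants per group at 90% power; a misplaced decimal is the likely cause

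*Protocol article*

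**What the plan says.** The planning values stand in one sentence of the protocol article, under Methods, Recruitment:

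- error rates: "where α=.05, β=.1"
- group 1 (ASB): "SD in group 1 (σ1) is 0.83" and "mean in group 1 (μ_1_) is 0.522"
- group 2 (PRF with OCP-DBBM): "SD in group 2 is (σ2) 0.044" and "mean in group 2 (μ_2_) is 0.42"
- allocation ratio: 1

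The result follows directly, with a citation to reference 13: "The total sample size required was 10 participants per group, as indicated by the calculation". The Abstract (Methods) plans the same number, 10 per group and 20 defects in all.

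The formula is a figure that is not shown in the text at hand. No sidedness is given with the calculation. The only sidedness in the article is in the Statistical Analysis section, for a different comparison: "paired 1-tailed *t* test or Wilcoxon signed-rank test for within-group comparison".

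Under Comparison With Prior Work, reference 13 is described as a study "comparing ASB and a mixture of autologous PRF and bioactive glass (PRF-BG) for regenerating periodontal infrabony defects". The same paragraph lists its three therapies as open flap debridement, PRF with bioactive glass, and ASB.

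**The concern.** The planned difference is 0.102, and the printed group 1 SD is about eight times as large (0.83 / 0.102 = 8.1). Ten participants per group cannot give 90% power for a difference that small relative to the spread. The two SDs also differ by a factor of about 19 (0.83 / 0.044), which is unusual for two arms measured on the same outcome.

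This is the only justification of sample size in the article. If 0.83 is the true SD, a non-significant between-group result would say almost nothing about whether the treatments differ. If 0.83 is a misprint, the design may stand, but no reader can reproduce the stated size from the published figures. The Limitations section mentions the small sample only as a limit on how widely the findings apply, so it does not alert the reader to either possibility.

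**Working it through.** **Inputs** (all from the sample size sentence): α = 0.05; power = 1 − 0.1 = 0.90; Δ = 0.522 − 0.42 = 0.102; σ1 = 0.83; σ2 = 0.044; ratio 1. Sidedness is not stated, so both versions are shown.

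**1. Attempt to reproduce the plan's figure.** The listed inputs are those of the two-mean formula with unequal SDs:

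n per group = (σ1² + σ2²)(z_α + z_power)² / Δ²

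- Sum of variances: 0.6889 + 0.001936 = 0.690836
- Δ² = 0.010404
- Two-sided: (1.960 + 1.282)² = 10.507, so n = 0.690836 × 10.507 / 0.010404 = 697.7, i.e. **698 per group**
- One-sided: (1.645 + 1.282)² = 8.564, so n = 0.690836 × 8.564 / 0.010404 = 568.6, i.e. **569 per group**

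Using the t distribution raises the two-sided figure to 699 (pooled) or 700 (Welch). Even one-sided at 80% power, the formula needs 411. The stated 10 is not reproduced.

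**2. What 10 per group gives with the printed SDs.** The standard error of the difference is √(0.690836 / 10) = 0.263, so the expected difference is 0.102 / 0.263 = 0.39 standard errors.

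| Two-sided 5% test, n = 10 per group | Pooled t | Welch t |
|---|---|---|
| Degrees of freedom | 18 | about 9 |
| Power | 6.6% | 6.4% |
| 95% CI half-width | 2.10 × 0.263 = ±0.55 | 2.26 × 0.263 = ±0.59 |

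A one-sided test has about 10% power. Either half-width is more than five times the planned difference.

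**3. Which σ1 would give 10?** Solving the two-sided normal formula for n = 10:

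σ1 = √(10 × 0.010404 / 10.507 − 0.001936) = 0.089

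That is close to 0.083, the printed value with the decimal point moved one place.

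**4. Result if σ1 were 0.083 (an assumption).** The sum of variances is 0.006889 + 0.001936 = 0.008825.

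| Method (two-sided, 90% power) | n per group | Power at 10 per group |
|---|---|---|
| Normal formula: 0.008825 × 10.507 / 0.010404 = 8.91 | 9 | 93.0% |
| Pooled t | 10 | 90.1% |
| Welch t | 11 | 89.0% |

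So 0.083 approximately reproduces the stated size, and matches it exactly only under a pooled t calculation.

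**The case against.** The strongest reply is that this is a misprint in one figure. With 0.083 the stated size comes out at 9 to 11 per group, so the design is sound and only the text needs correcting. Much of this stands. A reader might infer from the arithmetic that the trial needs 698 patients per group. The documents do not support that: 698 follows only if 0.83 is the true SD, and the misprint is the likelier explanation. The near-zero power belongs to that less likely case. The reply still concedes that the published line is wrong, and nothing else in the article gives another SD for group 1.

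Three further limits should be accepted:

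- A reader might say that 10 per group arises only with σ1 = 0.083. That is too strong. The normal formula gives 9 at that value and rounds up to 10 for σ1 from about 0.0835 to 0.089. As the formula is not shown, the method used is unknown.
- A reader might infer that the 0.42 comes from the PRF–bioactive glass arm of reference 13. The article does not say so. The citation is attached to the sample size result, and that study also had an open flap debridement arm. Which arms supplied the means is a question for the authors.
- The article does not state a two-sided pooled t test for this calculation, so that wording cannot be supplied on the authors' behalf. The unit is not settled either: the sample size sentence counts participants, the Abstract counts defects, and the inclusion criteria admit patients with one or two defects.

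The missing endpoint and unit for the means may be stated in a fuller protocol, and carries little weight alone. It is worth adding while the paragraph is being corrected.

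**Conclusion.** The point holds as an internal contradiction: the printed inputs, the 90% power and the 10 per group cannot all be right. As printed, the required size is about 70 times the stated one two-sided (698 / 10) and about 57 times one-sided (569 / 10). This conclusion does not depend on sidedness or on the choice between normal, pooled t and Welch t. It assumes only that the listed means, SDs and ratio feed a standard comparison of two independent means.

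That σ1 should read 0.083 is probable but unproven without the cited source. Under that reading, power at 10 per group is about 89% to 90% by t test with no losses. The stated size is then roughly right, with no margin: one loss per arm (9 per group) lowers pooled-t power to about 86%.

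Whichever SD is right, the relevance of the planning difference needs a sentence. None of the arms described for reference 13 is this trial's PRF plus OCP-DBBM group.

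**What to change.** Check σ1 against reference 13, then take one of two routes.

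- **If it is 0.083:** correct the figure. State the test and sidedness used in the calculation, the endpoint and unit the means refer to, and the resulting power (about 89% to 90% two-sided with 10 per group and no losses, depending on the t test).
- **If it is 0.83:** withdraw the 90% power claim, restate two-sided power as about 6% to 7% for a difference of 0.102, and present the between-group comparison as exploratory, with estimates and confidence intervals.

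In both cases, state which arms of reference 13 supplied 0.522 and 0.42, and why that difference is a reasonable guide for a PRF plus OCP-DBBM comparator.

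The cost is one look at the source and one rewritten paragraph. Enrolment does not change.

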Both osteoconductive and osteoinductive qualities are present in the new gold standard for xenografts, macropore octacalcium phosphate–coated deproteinized bovine bone.

This is made from a 100% bovine cancellous bone substitute. Because graft bone materials have a high osteoconductivity, they aid in the proliferation of osteogenic cells and microvessels, which in turn stimulate the formation of new bone [8].

To facilitate the successful regeneration of damaged periodontal tissues, autologous sticky bone (ASB) was introduced as an alternative. ASB is defined as a physiologically solidified bone graft that is embedded in the fibrin network. Strong interconnection of particle bone powders by the fibrin network prevents scattering, even when shaken with a cotton plier. Sticky bone offers many benefits: (1) it can be shaped to suit virtually any kind of bony defects; (2) it prevents the grafted bone from moving; (3) no biochemical additives are needed to maintain the volume of augmentation during the healing period, thereby minimizing the need for block bone and titanium mesh; (4) fibrin accelerates bone and soft tissue regeneration by entrapping platelets and leukocytes that release growth factors; and (5) fibrin interconnection minimizes soft tissue ingrowth into the sticky bone graft [9].

One of the newest developments in regenerative surgery is the use of platelet concentrates for in vivo tissue engineering applications: the first two are platelet-rich fibrin (PRF) and platelet-rich plasma. Platelet concentrates, a concentrated solution of growth factors produced from platelets, are applied as a bioactive surgical adjuvant to facilitate the healing of wounds [10].

As radiographs can identify the quantity and type of damage to the alveolar bone, they play a significant role in periodontal diagnostics. Further research comparing radiographs to presurgical measures found that “bone loss can be underestimated by 1.5 mm, with considerable differences in examiners’ interpretations” [11].

Computed tomography scans have been explored for their potential in highly accurate 3D image alignment. However, they have limitations, including significant radiation exposure and the bulkiness and expense of the equipment [12]. Cone-beam computed tomography (CBCT) has recently emerged as a viable technique in dentistry, offering a lower-cost alternative to traditional computed tomography while still producing high-quality pictures and exposing patients to less radiation.

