#### Preparation of ASB

Following complete debridement, an 18G needle will be used to draw about 30 mL of venous blood from the patient’s forearm using 1 of 2 vacutainer types: (1) noncoated for autologous fibrin glue and (2) glass coated for concentrated growth factor (CGF) and alternated controlled centrifugation at 2400 rpm to 2700 rpm will be performed for 12 minutes. The autologous fibrin glue obtained will then be mixed with OCP-DBBM for polymerization, which produces a yellow, sticky bone. CGF will be mixed with the prepared sticky bone to produce the CGF–sticky bone mixture.

#### Procedure for Group 1

Complete isolation and hemostasis of the defect will be achieved. The flap will be presutured without tying the knot to allow rapid flap closure after placement of graft material. ASB will be placed into the osseous defect at the test site with light pressure until it is filled to the most coronal level of the osseous wall by raising the flap. The flap will then be coronally repositioned and sutured in such a way that the flap margin will be located 1 mm to 2 mm coronal to the cemento-enamel junction (CEJ), ensuring primary flap closure. A combination of vertical mattress and interproximal sutures (4-0 nonresorbable surgical sutures, braided black silk [Mersilk, Ethicon; Johnson & Johnson Ltd]) will be used to secure the flap in position. Slight pressure will be applied to the area with saline-soaked gauze for approximately 2 minutes to adapt the soft tissue well to the tooth surface and eliminate any space in which a clot might form and disrupt reattachment. The surgical site will be dressed with a periodontal dressing (Coe-Pak, GC Inc) on the buccal and lingual aspects.

#### Procedure for Group 2

The surgical procedure for the defect site will be identical to the procedure of the test site, except that osseous defects at group 2 sites will be packed with OCP-DBBM, and then a PRF membrane will be placed over the bone graft.

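### The 90% power for ASB versus PRF plus OCP-DBBM rests on planning values credited to a study with no PRF plus OCP-DBBM arm, and the printed inputs do not give it either

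*Protocol article*

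**What the plan says.** The sample size paragraph under Recruitment in the protocol article gives "where α=.05, β=.1, SD in group 1 (σ1) is 0.83", a group 1 mean of 0.522, a group 2 SD of 0.044, and "mean in group 2 (μ_2_) is 0.42, and ratio (group 2 to group 1)=1". It then concludes: "The total sample size required was 10 participants per group, as indicated by the calculation [13". That reference is the only source given. The article does not print a power of 90%; it follows from β=.1.

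Comparison With Prior Work describes the cited study: "they tested 3 therapies (open flap debridement [OFD], PRF-BG, and ASB".

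In this trial, Preparation of ASB says that the group 1 graft is made by mixing autologous fibrin glue with OCP-DBBM. Procedure for Group 2 says that "osseous defects at group 2 sites will be packed with OCP-DBBM, and then a PRF membrane will be placed over the bone graft". Both arms therefore receive OCP-DBBM. The article gives no reason for carrying the earlier study's difference over to this contrast.

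**The concern.** A power statement holds for the contrast and the variances it was computed from. Here the difference of 0.102 is credited to a study that, as the article itself describes it, had no PRF plus OCP-DBBM arm. A difference between ASB and an arm with another graft, or with none, can include a graft effect. Giving OCP-DBBM to both groups may remove some of that effect, or may not. Either way, the stated β=.1 has no quantitative basis for the randomized comparison.

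The size of the difference matters because, with 10 per group, power changes steeply with it. The matter is also separate from the printed SD. Someone who corrected only the SD could believe that 90% power had been restored, while the mean difference remained unsupported.

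**Working it through.** **Inputs.** From Recruitment: α=.05, β=.1, μ1=0.522, σ1=0.83, μ2=0.42, σ2=0.044, ratio 1, n=10 per group. Difference: 0.522 − 0.42 = 0.102. The sidedness of the sample size test is not stated, so two-sided is assumed and one-sided is shown as a check. No dropout allowance is stated, so none is applied.

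**1. Reproducing the plan's figure from the printed inputs.** n per group = (z₀.₉₇₅ + z₀.₉₀)² (σ1² + σ2²) / (μ1 − μ2)².

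- (1.960 + 1.2816)² = 10.507
- σ1² + σ2² = 0.6889 + 0.001936 = 0.690836
- n = 10.507 × 0.690836 / 0.010404 = 697.7, so 698 per group

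One-sided it is 569. At 80% power it is 522 two-sided and 411 one-sided. The stated 10 is not reproduced.

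**2. Power with 10 per group on the printed inputs.** SE = √(0.690836/10) = 0.263 and the noncentrality is 0.102/0.263 = 0.388. The pooled t test on 18 df has power 6.6%; with Welch df it is 6.4%. The one-sided figure is about 10%.

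**3. What would give 10.** Assume σ1 = 0.083. This value is not in the documents.

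- σ1² + σ2² = 0.006889 + 0.001936 = 0.008825
- n = 10.507 × 0.008825 / 0.010404 = 8.9, so 9 by the normal formula, 10 by the pooled t and 11 by Welch
- SE = √(0.008825/10) = 0.0297; power at n=10 is 90.1% (pooled t) or 89.0% (Welch)

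So 10 per group fits 0.083 and does not fit 0.83.

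**4. Sensitivity to the group 2 mean.** n=10 per group, two-sided α=.05, pooled t, μ1=0.522 and σ2=0.044 held fixed:

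| Group 2 mean | Difference | Power, σ1=0.083 (assumed) | Power, σ1=0.83 (printed) |
|---|---|---|---|
| 0.40 | 0.122 | 97% | 7.2% |
| 0.42 | 0.102 | 90% | 6.6% |
| 0.44 | 0.082 | 74% | 6.0% |
| 0.47 | 0.052 | 38% | 5.4% |

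**5. Expected precision.** The 95% CI half-width is t₀.₉₇₅,₁₈ × SE: 2.101 × 0.0297 = 0.062 if σ1=0.083, and 2.101 × 0.263 = 0.55 if σ1=0.83. The first is about 60% of the planned difference of 0.102; the second is more than five times that difference.

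**The case against.** Borrowing from the nearest related trial is ordinary planning when no result exists for the exact comparator, and the cited study did compare ASB with PRF plus a bone substitute. That the 0.42 came from one of its arms is an inference: the article cites the study for the calculation and does not name the arm, outcome or unit. The derivation may be set out in a fuller document. These points stand, so the absence of that detail is not pressed here. They do not rescue the power claim. The article itself prints the inputs, the β and the single source, and no arm it describes for that source matches group 2.

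A reader might infer that the shared graft must narrow the difference, so that true power is below 90%. The documents do not support this. The text that seems to help is "Both osteoconductive and osteoinductive qualities are present in the new gold standard for xenografts, macropore octacalcium phosphate–coated deproteinized bovine bone" under Background, but it ranks OCP-DBBM among xenografts and says nothing about OCP-DBBM against bioactive glass. The Discussion points the other way: it calls OCP-DBBM's efficacy relatively lower, though it is speaking of the material without autologous growth factors, and it expects ASB to do better. The group 1 mean is uncertain too, because the documents do not say which graft the earlier ASB arm used. A lower group 2 mean would raise power, as the row for 0.40 shows.

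It is also fair to say that on the printed SD the choice of comparator hardly moves power, from 6.6% to 5.4% when the difference is about halved. The SD is the larger numerical fault. The comparator problem becomes material once the SD is corrected to something that yields 10 per group.

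**Conclusion.** The point holds in this form: β=.1 is unsupported for ASB versus PRF plus OCP-DBBM. The only source cited had, by the article's own account, no such arm, and no argument is given for carrying its difference over. This does not show that the trial has less than 90% power for a given true difference in bone fill; the documents cannot say which way the error runs.

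In size: on the inputs as printed, 10 per group gives about 7% power at the planned difference, so the 90% does not follow for any comparison with these values. If σ1 is assumed to be 0.083, the 90% is recovered at a group 2 mean of 0.42, but it moves to about 97% at 0.40, 74% at 0.44 and 38% at 0.47. Apart from the results at the printed SD, these figures rest on that assumed SD, on μ1=0.522 and σ2=0.044 holding in this trial, and on a two-sided pooled t test.

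**What to change.** Keep 10 per group and restate the sample size paragraph:

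1. Check σ1 against the source, then correct or confirm it.
2. Withdraw the claim of β=.1 for this comparison, and say that the planning values come from a study without a PRF plus OCP-DBBM arm.
3. Give power at n=10 per group over group 2 means on both sides of 0.42, using the verified SDs. If σ1 proves to be 0.083, the figures are about 97% at 0.40, 90% at 0.42, 74% at 0.44 and 38% at 0.47.
4. Add the expected 95% CI half-width for the between-group difference: about ±0.06 if σ1 is 0.083, about ±0.55 if 0.83 is right.

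The cost is a wording change, with no extra patients or procedures. The downside is that the stated power becomes less favourable or less certain.
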